## 4.5 Patients

### 4.5.1 Inclusion criteria

(1) Volunteer patients with good compliance and ranging from 18 to 70 years.

(2) Patients meeting these following conditions:

- Tumor has been removed completely via evaluations.
- The pathological diagnosis is HCC.
- The maximum diameter of a single tumor is less than or equal to 10cm and greater than or

equal to 2cm.

- The number of the tumor is less than three and the maximum diameter is less than or equal to 5cm regarding multiple nodule.
- No macroscopic vessel invasion.

(3) Other functions of organs are normal.

(4) KPS is over 70.

(5) Child-pugh stage A.

(6) The latest results of laboratory tests should meet these following standards:

- $HgB \geq 9.0g/dl$ .
- The count of neutrophils is more than 1,500/mm.
- The count of platelets is more than 50,000/ul.
- The levels of ALT and AST are lower than or equal to twice normal ceiling values.
- The level of serum creatinine is less than or equal to 1.5 times normal ceiling values.

(7) The HCG test of women with fertility should be negative within 14 days before treatment.

(8) Patients who meet all the above conditions sign written informed consents.

#### 4.5.2 Exclusion criteria

(1) Patients under 18 or over 70.

(2) Pregnant women or women in lactation.

(3) Poor physical conditions and liver functions (Child-pugh stage B and C, refractory ascites and brain diseases).

(4) Severe brain, lung, kidney and hematological diseases.

(5) Any unstable factors or factors affecting subjects' safety or compliance.

(6) Patients with known or doubtful allergic to iodine.

(7) Patients received other treatment for tumor before surgeries (such as liver transplantation, TACE, local ablation for HCC, chemotherapy, radiotherapy and etc.).

(8) Patients participating in other trials.

(9) Patients with heart diseases: CHF>NYHA stage 2, coronary atherosclerotic heart disease, arrhythmia or treated arrhythmia with medicine (digoxin or  $\beta$ -receptor blocker were allowed) and refractory hypertension.

(10) Severe active infections.

(11) Epilepsy treated with medicine.

(12) Patients who have received allograft transplantations.

(13) Patients with history of other tumor except that he or she have been cured 3 years before the study.

(14) Patients with history of bleeding or susceptibility to bleeding.

(15) Patients meanwhile receiving dialysis.

(16) Recurrent HCC.

## 5. Method

### 5.1 Radionuclides

#### 5.1.1 $^{125}I$

$^{125}I$  is produced in Reactor Engineering Research of China Institute of Atomic Energy with 0.8mm  $\times$  4.5mm and a half-life of 59.6 days and enveloped with Nickel titanium alloy. It is sterilized under high temperature. It has X-ray with energy of 27.4-31.5Kev and  $\gamma$ -ray with energy of 35.5

Kev. The activity of per seed is 0.5-0.6mCi.

## **5.2 Treatment and doses**

### **5.2.1 Hepatectomy**

The extents of resection depended on volumes and positions of tumor, estimated rest liver volumes and stages. Standard approaches for surgery will be adopted, such as hemihepatectomy, heplobectomy, hepatic segmentectomy and wedge resection of the liver, which are via finger pinching or jaws. During resections, the incisional margins should be over 1cm and ultrasonography was routinely utilized. The wounds will suture or cover with the free omentum. Double cannula drainage will be placed next to the wounds after the surgeries.

### **5.2.2 Interventions of two groups after removal of the tumor**

I group: The wound will be carefully stanch after the tumor has been removed completely. The square meter of the wound will be measured and the data will be input into the computer to determine the number of radionuclides implanted and doses. Mick radionuclide applicator will be used to implant I at 1cm interval in the normal liver tissues at the incisional margin (I was produced in Reactor Engineering Research of China Institute of Atomic Energy with 0.8mm×4.5mm and a half-life of 59.6 days and enveloped with Nickel titanium alloy. It is sterilized under high temperature. It has X-ray with energy of 27.4-31.5Kev and γ-ray with energy of 35.5 Kev. The activity of per seed is 0.5-0.6mCi. The prescription dose was 160Gy). Ultrasonography is utilized to see whether seeds are well-distributed. More seeds will be implanted so as to avoid cold spot areas if seeds are not well-distributed. Fibrin gel will be smeared on wounds and then sutured with absorbable gelatin sponge or hemostatic gauze to prevent I from dropping off. The rest treatment of the control group is the same as that of the I treated group except for implantation of I. Both of the groups will receive identical routine support treatment for the liver after surgeries.

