### **7.2 Custody and distribution systems**

7.2.1 The radioactive seeds should be kept by the person responsible for the custody in accordance with national drug regulations.

Registration statistical forms should be established with serious filling and permanent preservation.

If the product is found lost after being marked, it should be immediately traced and reported to the higher authorities.

Before the product is used for patients, the name of the seeds, patient's name and dosage should be strictly and carefully checked.

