## **9. Follow-up**

Patients must be arranged for close follow-up which included rechecks every 2-3 months or contact by phone after entering the treatment group.

Follow-up will be carried out according to the following stipulations with CRF filling:

Every 2 to 3 months: blood routine, liver and kidney function, AFP, liver ultrasonography;

Every 3 to 4 months: enhanced abdominal CT or MRI.

Every six months: chest X-ray or chest CT;

If the patient had signs of distant metastases of the lung, bone, intracranial, whole-body bone scan, CT of other parts, and even PET-CT should be added.

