### **10.4 Objective evaluation of efficacy**

According to the results of B ultrasound, CT or enhanced MR, chest CT and other imaging studies, recurrence would be assessed.

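### The protocol recognises that implanted seeds may come loose, but plans no detection, count or recording of seed loss after surgery, and its adverse-event window appears to close before the first follow-up image.

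*Protocol*

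**What the plan says.** **Risk and prevention.** Section 5.2.2 (repeated in 4.3) has the wound covered after implantation: "Fibrin gel will be smeared on wounds and then sutured with absorbable gelatin sponge or hemostatic gauze to prevent" seeds from coming loose.

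**Position check.** The same section says "Ultrasonography is utilized to see whether seeds are well-distributed". The action tied to it is "More seeds will be implanted so as to avoid cold spot areas if seeds are not well-distributed", which places the check inside the operation.

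**Follow-up imaging.** Section 9 sets liver ultrasound every 2 to 3 months, then "Every 3 to 4 months: enhanced abdominal CT or MRI" and "Every six months: chest X-ray or chest CT". Section 8.2 also lists imaging at intervals of 2 to 3 months, at the treating or a local hospital. Neither section asks for seed number or location.

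**Use of the images.** Section 10.1 uses abdominal CT or MRI to find new liver lesions and chest films to find lung metastasis. Section 10.4 names the imaging methods, ending "chest CT and other imaging studies, recurrence would be assessed".

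**Safety collection.** Section 11 counts any adverse medical event, whatever its cause, from consent until a month past the end of treatment. Section 11.3 reports serious events within 30 days of treatment, defined by death, threat to life, hospitalisation or disability. Neither names seed loss or displacement.

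**Custody.** Section 7.2 says "If the product is found lost after being marked, it should be immediately traced and reported to the higher authorities".

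**The concern.** Loss or displacement of a seed is a harm specific to this implant, and the protocol itself takes steps against it. Objective 1 in section 2 includes safety, and objective 2 is a standardised 125I protocol for others to use. Both need to know how often seeds fail to stay in place.

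As written, that information has no planned route into the data. No step after the operation looks for a missing or displaced seed, and no rule says to record one seen by chance after the adverse-event window. A final report of no seed loss could then mean that seeds stayed in place or that the question was never asked, and a reader could not tell which. An analysis plan cannot repair this later, because the data would not exist.

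**Working it through.** The protocol gives no figure for seed number per patient or for seed loss, so there is no stated result to reproduce on this point. The check is a comparison of dates, plus one decay calculation.

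**Inputs**
- Half-life of 59.6 days (section 5.1.1).
- Adverse-event window: one month past the end of treatment (section 11); serious events 30 days (section 11.3).
- First scheduled images: ultrasound at 2 to 3 months, abdominal CT or MRI at 3 to 4 months, chest imaging at 6 months (section 9).
- Assumptions: implantation, a single act, is the end of treatment; a month is 30 days.

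**Formula.** Activity remaining at day t = 0.5^(t/59.6). This is also the share of all decays still to come.

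| Day | Protocol event | Remaining | Already decayed |
|---|---|---|---|
| 30 | Adverse-event window closes | 0.705 | 0.295 |
| 60 | Earliest ultrasound | 0.498 | 0.502 |
| 90 | Latest first ultrasound; earliest abdominal CT or MRI | 0.351 | 0.649 |
| 120 | Latest first abdominal CT or MRI | 0.248 | 0.752 |
| 180 | First chest image | 0.123 | 0.877 |

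**Reading the dates.** The earliest scheduled image falls at least 60 - 30 = 30 days after adverse-event collection ends. No scheduled follow-up image lies inside the window. About 71% of the decays are still to come when the window closes.

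**Do other provisions fill the gap?**
- The section 7.2 duty depends on a product being found lost. It sits among custody rules and creates no check in the patient.
- Section 12.2 has inspectors verify the supply, storage, distribution and return of trial materials, and section 13.3 keeps distribution records. Both account for stock, not for seeds already implanted.
- Section 11.2 follows adverse events to resolution, but only events that have already been recorded.
- A displaced seed without symptoms meets none of the serious-event criteria in section 11.3.

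**The case against.** The strongest reply is that the record is less bare than it looks. Sections 10.1 and 10.4 define how recurrence is established; they do not forbid a radiologist from reporting anything else. Metal-enveloped seeds could well be noticed on follow-up films. The adverse-event definition is broad, so a recognised event in the first month would be captured. CRF filling instructions are mentioned in section 13.1 but are not shown, and nor is the flow diagram.

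Much of this stands, and it limits the point. A reader might infer that lost seeds must go undetected, that the section 7.2 duty could never be triggered, or that every loss would go unrecorded. The text does not support that: a chance finding or a symptomatic early event could be reported. What it supports is that detection and recording are not planned.

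A reader might also infer that many patients would lose many seeds, so that cold areas at the margin would be confused with treatment failure. The documents give neither a seed count nor a loss rate, so the scale cannot be derived, and the log-rank comparison between groups in section 13.2 needs no seed count. Likewise, section 5.2.1 says "Double cannula drainage will be placed next to the wounds after the surgeries" but does not present the drains as a route of seed loss. Movement of seeds to the chest is not named anywhere.

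The last objection is that this is a mere omission. It is more than that, because the stated adverse-event window sets a limit that leaves out findings on every scheduled scan.

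**Conclusion.** The point holds in limited form. The protocol recognises that seeds may come loose and plans no postoperative detection, count or recording of it. With implantation as the end of treatment, adverse-event collection closes at least 30 days before the first scheduled follow-up image, with about 71% of seed activity remaining. A displaced seed seen by chance on a later scan need not be recorded, so a report of none would be uninformative for the safety objective.

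The timing depends on reading implantation as the end of treatment, which section 11 does not define. A later end point would move the window and could bring some scans inside it, but those scans would still carry no request to look for seeds. The point concerns safety data. It makes no claim about how often seeds are lost or about bias in time to recurrence. It should be corrected, at low cost.

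**What to change.** - **Section 9.** Have the abdominal and chest images already scheduled in the 125I group also read for visible seeds outside the implanted margin and, where the modality allows, for seed number against the number implanted. Enter the result on the CRF.
- **Section 11.** Make seed loss or displacement a recorded adverse event whenever it is found, not only in the first month, and link it to the trace-and-report duty in section 7.2.

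This changes data capture only: no added scans and no change to treatment. It costs a little more reading time. Counts will be incomplete where MRI is used or where a local hospital does not hold the implanted number. Early losses will be found late, because the first scans come at 2 to 4 months.

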## **6. Concomitant medication**

The use of drugs or treatment during the study period

The use of concomitant drug and treatment during the study period according to the need is as follows:

- When the test drug induced adverse effects or the disease is in need of treatment, drugs can be given for relieving the symptoms.
- When the subjects vomite, which is caused by chemotherapy drugs, the antiemetic can be given.
- When the pain of subjects influenced sleep and rest, painkillers can be given.
- When the subjects have constipation, diarrhea, insomnia and other symptoms because of other reasons, drugs can be given for relieving symptoms.
- When the subjects have anaphylactoid reactions, HAMA response and infusion reactions, dexamethasone can be given.
- Furosemide could be used.
- Routine liver protecting and immune improving drugs can be use.
- Antiviral drugs can be used for anti-viral treatment.
- Routine postoperative treatment, such as TACE, PEIT, and local ablation therapy can be carried out.

All the simultaneously used drugs should be detailed recorded in CRF, and described.

## **7. Management of test chemicals**

### **7.1 Management of I seeds**

- a) Radioactive particles must be used by experienced physicians in hospitals with relevant qualifications.
- b) The seeds should be strictly in accordance with the indications and usage of the program recommending dosage range, which was not free to be changed.

### **7.2 Custody and distribution systems**

7.2.1 The radioactive seeds should be kept by the person responsible for the custody in accordance with national drug regulations.

Registration statistical forms should be established with serious filling and permanent preservation.

If the product is found lost after being marked, it should be immediately traced and reported to the higher authorities.

Before the product is used for patients, the name of the seeds, patient's name and dosage should be strictly and carefully checked.

7.2.2 The procedure of preservation and distribution

Each patient of the group will obtain a random number, and then the number will be reported to the preservers of the center by the researchers. The preservers would judge whether to use seeds which will be distributed to the patients with the corresponding number.

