## 4.3 Grouping

All of the patients will be grouped after receiving curative surgeries for HCC.

$^{125}\text{I}$  treated group: The wound will carefully stanch after the tumor have been removed completely. The square meter of the wound will be measured and the data will be input into the computer to determine the number of radionuclides will implant and doses. Mick radionuclide applicator will be used to implant  $^{125}\text{I}$  at 1cm interval in the normal liver tissues at the incisional margin ( $^{125}\text{I}$  was produced in Reactor Engineering Research of China Institute of Atomic Energy with  $0.8\text{mm} \times 4.5\text{mm}$  and a half-life of 59.6 days and enveloped with Nickel titanium alloy. It is sterilized under high temperature. It has X-ray with energy of 27.4-31.5Kev and  $\gamma$ -ray with energy of 35.5 Kev. The activity of per seed is 0.5-0.6mCi). Ultrasonography is utilized to see whether seeds are well-distributed. More seeds will be implanted so as to avoid cold spot areas if seeds are not well-distributed. Fibrin gel will be smeared on wounds and then sutured with absorbable gelatin sponge or hemostatic gauze to prevent  $^{125}\text{I}$  from dropping off.

Control group: The rest treatment will be the same as that of the  $^{125}\text{I}$  treated group except for implantation of  $^{125}\text{I}$ .

Both of the groups received identical routine support treatment for the liver after surgery.

All of the patients will receive venous blood collection on one day before surgeries and day 7 after surgery. Aminotransferase and bilirubin were measured. AFP and MMP-9 will be measured via radioimmunoassay. Meanwhile, activity of nature killer cells and T cell subsets will be measured by flow cytometers (America COULTER). Curative hepatectomy of HCC must meet these following conditions: a. Tumor is completely removed. Explorations during surgery show no tumor remaining and fast pathology results revealed that there are no cancer cells in the incisional margins. b. There are no macroscopic cancer emboli in the main side branches and bile duct bifurcations. c. The number of the tumor is less than three. d. There is no extrahepatic metastasis.

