## 4.4 Randomization

Patients included in the study will be allocated randomly. Random digits will be generated by computer. Custody of the random number table by hand.

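### The allocation procedure in sections 4.4 and 7.2.2 does not ensure that assignment is concealed

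*Protocol*

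**What the plan says.** Two short sections of the protocol set out the procedure.

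- **Section 4.4 (Randomization).** "Random digits will be generated by computer". On safekeeping it says only "Custody of the random number table by hand". It names no holder and does not separate the table from recruiting staff.
- **Section 7.2.2 (preservation and distribution).** A trial participant "will obtain a random number, and then the number will be reported to the preservers of the center by the researchers". On what the custodians do next, it says: "The preservers would judge whether to use seeds which will be distributed to the patients with the corresponding number".

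Two other sections bear on when this happens. Section 4.3 states: "All of the patients will be grouped after receiving curative surgeries for HCC". Sections 4.3 and 5.2.2 nevertheless place implantation within the operation, starting from the point where "The wound will be carefully stanch after the tumor has been removed completely". Neither describes a sham procedure or blinding: the control group has the same treatment without seeds.

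**The concern.** Randomisation protects the comparison only if the people who enrol patients can neither foresee nor influence the next assignment. Here the number reaches the research team first, and that team carries it to the custodian. The step from number to arm is described with the verb *judge* and without a rule. Because seeds are visibly implanted or not, the operating team learns the arm of every number it has reported.

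If staff could foresee or influence the arm, patients with a better outlook, such as those with a small or single tumour, could end up disproportionately in the 125I group. That would favour 125I on both time to recurrence and overall survival. With 68 patients in total, a shift of a few patients matters.

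**Working it through.** No figure in the protocol tests this point, so the check is mainly textual.

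**Step 1. What a concealed procedure needs, against what is written.**

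| Requirement | Protocol text |
|---|---|
| Unpredictable sequence | Computer-generated digits (4.4) |
| Named list holder, independent of recruitment | Table kept by hand, holder not named (4.4) |
| Fixed arm for each number | No rule; custodians judge seed use by the number (7.2.2) |
| Patient registered before the number is obtained | Not required in 4.4 or 7.2.2 |
| Recruiters unable to link number and arm beforehand | Researchers hold and relay the number (7.2.2); access to the table not addressed |

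Only the first requirement is met by the text.

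**Step 2. Is there room to act on a known number?** Complete removal and a pathological diagnosis of HCC are inclusion conditions (4.5.1), and clear margins on fast pathology are part of the definition of curative resection (4.3). These are settled at or after resection. Section 4.3 puts grouping after surgery, while seeds are placed during the operation. The point at which the number is obtained, relative to these conditions, is therefore not fixed.

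**Step 3. Illustration of what an imbalance would do.** Taken from section 4.2: 68 patients, control median 18 months, follow-up 5 years (60 months). Assumed: 1:1 allocation (68 / 2 = 34 per arm), exponential times, no treatment effect, a 40% share of high-risk patients overall with hazard ratio 2 or 3 against the rest, and the degree of imbalance. Analysis: log-rank test, counting a false win for 125I when z < -1.96. There were 4,000 to 6,000 simulated trials per scenario.

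Patients moved: a balanced arm has 0.40 × 34 = 13.6 high-risk patients. A 50%/30% split gives 17.0 and 10.2, a shift of 3.4 per arm. A 55%/25% split gives 18.7 and 8.5, a shift of 5.1 per arm.

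| Hazard ratio of high-risk patients | High-risk share, control / 125I | Apparent HR | False wins |
|---|---|---|---|
| 2 | 40% / 40% | 1 | about 3% |
| 2 | 50% / 30% | 0.88 | about 7% |
| 2 | 55% / 25% | 0.82 | 11% to 12% |
| 3 | 50% / 30% | 0.83 | about 11% |
| 3 | 55% / 25% | 0.74 to 0.76 | 18% to 19% |

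Under the one-sided 5% test named in section 4.2, false wins in the four unbalanced scenarios run from about 12% to 30%. The table shows the consequence of a given imbalance. It does not show that this procedure would produce one.

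**The case against.** A reader might infer that assignment is not concealed. The documents do not support that.

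- Holding a number is not knowing the arm. If only the custodians hold the key, section 7.2.2 describes a form of third-party allocation. No section says that researchers can see the table.
- *Judge*, tied to the corresponding number, may simply mean looking up the arm. Section 4.4 says that allocation is random, which points to a pre-set assignment. Keeping the table by hand does not mean that recruiters keep it.
- Decoding the key from past cases requires a simple rule such as odd/even. The protocol states no such rule.
- Clean margins could not be used for steering, since section 4.3 requires them of every patient.
- It would also go too far to say that the analysis could neither detect nor undo the bias. Tumour size and number are assessed for eligibility (4.5.1), and section 13.2 plans group comparisons and Cox regression. Imbalance in measured factors could be seen and partly adjusted for; selection on unmeasured factors could not.
- Other controls exist: a check of patient name and dosage before seeds are used (7.2.1), monitoring of consent, screening and subject identification (12.2), and retained seed distribution records (13.3). They make swapped or dropped patients traceable.

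All of this stands, and it limits the conclusion. It does not supply what is missing. The traceability controls act after the event, and the favourable readings of 7.2.2 are possible but not stated. Nor is this detail that can wait for a statistical analysis plan: sections 4.4 and 7.2.2 are where this protocol sets out its allocation procedure.

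**Conclusion.** The point holds in limited form: the written procedure does not ensure concealment. The list holder, access to the list, the number-to-arm rule and the moment of registration are left open, in a trial without described blinding and with some eligibility settled only at resection. That leaves room for selection bias in time to recurrence and overall survival.

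The size of any bias is unknown. The simulated hazard ratios of 0.74 to 0.88 depend on assumed prevalence, risk ratio, degree of imbalance and 1:1 allocation. The mildest case, 0.88, is modest beside the design hazard ratio of 0.5. The flow diagram in section 3 was not available in the text and could add a detail. This is an inexpensive improvement that should be made, not evidence that allocation was compromised.

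**What to change.** Rewrite sections 4.4 and 7.2.2 so that:

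1. The computer list fixes the arm for each consecutive number and is prepared by someone who does not treat trial patients.
2. Only the seed custodian holds it, in sequentially numbered, sealed, opaque envelopes or an equivalent concealed list.
3. The researcher first reports the patient's identity and confirmed eligibility. The custodian logs this with date and time, and from then on the patient counts as irrevocably registered.
4. Only then does the custodian release the next assignment in order and issue or withhold seeds as listed. This rule replaces the wording about judging.
5. The log is reconciled with the seed distribution records kept under section 13.3.

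State the moment of release, and which eligibility conditions must be settled by then. Sections 4.3 and 5.2.2 must be reconciled on the timing of grouping and implantation for this to be possible.

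Cost: protocol wording and a set of envelopes or equivalent. The custodian and the distribution records already exist. The downside is one extra logged step before seeds are issued.
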